### Analyses WP2

The content-analytical data evaluation of the audio-recorded and verbatim transcribed pseudonymised data will be carried out using the software MAXQDA [46] in a content-structuring procedure [47] by a multi-professional study team (e.g., GPs, patient representatives, psychology, social science, public health). Content-structuring qualitative content analysis is, in addition to evaluative and type-forming qualitative content analysis, a procedure of category-based methods for the systematic analysis of qualitative data [47]. These evaluation procedures on category-based methodology is a language-related, rule-guided systematic scientific method with the aim of pragmatic reduction of complexity [47].

### Current status

At the time of submission of this protocol, the data collection has been completed. The analyses of GP data have also been completed, analyses of patient data are still being conducted.

### WP3: Systematic development of the GP training

WP3 focuses on the synthesis of results from WP1 and WP2 to inform the systematic development of a brief, single-session, tailored GP training on the delivery of PA advice to people with IHD according to the 3As method.

In a strategy workshop, results of WP1 and WP2 will be compared and connected, using visual representations (e.g., acyclic behaviour change diagrams [48]), discourse and expert consensus techniques.

The interdisciplinary study team, comprising experts in research on behaviour change, health services and public health, will develop a training manual in collaboration with GPs and patient representatives, with provisions for future adjustments for sustainability, such as online booster modules and good practice videos. The COM-B (capability, opportunity, and motivation-behaviour) model [35] will serve as theoretical framework for the development of the training, and the behaviour change taxonomy (BCT) will be used to describe active elements of the training [28]. According to COM-B, the interplay between capability (C), opportunity (O), and motivation (M) influence behaviour (B), and a specific behaviour in turn influences these factors [35]. The training will be developed to address “capability and motivation” by providing knowledge and practical skills to deliver PA advice. By using the 3As (ask/assess, advise, assist) method as a very brief, less time-consuming method of delivering advice, which can be more easily integrated into daily practice, the training will also aim to influence “opportunity”. The definition and description of potentially active training elements according to the BCT [28] will also be part of WP3. Training materials and case vignettes for simulated role-plays using simulation patients will be developed in collaboration with the “communication in medical education” team of the Heinrich-Heine University. Experienced GPs and peer-trainers from the study institute will review the training manual and didactic methods.

### Current status

At the time of submission of this protocol, a first draft of a training manual has been developed as described above.

### WP4: Accompanying health economic research

WP4 aims at developing a (web-based) discrete choice experiment (DCE) which will identify preferences regarding IHD patients’ outcomes on increased PA, and to develop a questionnaire that accurately assesses health care utilisation in people with IHD. Findings of WP4 will thus help to inform future RCTs by providing the most preferred patient-relevant outcomes for PA based interventions and to inform future health economic evaluations. The development of the DCE will adhere to recent recommendations [49].

First, a literature review and eight to twelve qualitative semi-structured individual interviews with people with IHD based on an interview guide will be conducted to identify relevant outcomes on increased PA. Second, these identified outcomes will be discussed with experts (e.g., people with IHD, GPs, cardiologists) in a joint workshop. In addition, the findings on relevant patient outcomes will be considered in the process of training refinement described in WP5. The experts will select the most important outcomes that will be used as attributes in the DCE. Alongside, a health care utilisation questionnaire will be developed based on a literature review and previous work by members of the study team [50].

The DCE will be pilot tested in people with IHD of the pilot study (see WP5, *N* = 120), and evaluated in patients of the control group of the main cluster randomised controlled trial (cRCT) (WP6, *N* = 300). The health care utilisation questionnaire will be pilot tested in patients of the control group of the main cRCT. IHD patients will receive a printed version of the questionnaires as well as a link enabling them to fill in a web-based version, alternatively. This will help to estimate the acceptance of different modes of assessment and to choose the optimal mode of assessment for the evaluation of the DCE which will follow in WP6 (*n* = 300). To avoid influences on the main study outcomes of the cRCT in WP6, patients will be asked to complete the DCE and health care utilisation questionnaires at home, following the collection of the primary and secondary outcomes of the cRCT.

### Analyses WP4

Transcribed individual interviews will be analysed by qualitative content analysis. Outcomes will be identified according to the suggested criteria for patient-relevant outcomes by Nano et al. [51]. Preference weights of the DCE will be derived by a conditional logit regression model and by latent class analysis considering preference heterogeneity. Health care utilisation data will be analysed descriptively by means, standard deviations, and distributions of quantities.

### Current status

At the time of submission of this protocol, WP 4 is still ongoing.

## Phase II) Piloting of the intervention study and of the main evaluation study

### WP5: Pilot study

Based on preliminary work of the study team [22] and as recommended according to the MRC framework [31], a feasibility study testing the practicality of the planned evaluation study (WP6) is not considered necessary. Instead, a pilot study will be carried out to evaluate implementation outcomes, including the training of GP peer trainers, recruitment and randomisation processes, content and schedule of the training, materials, methods of data collection among patients and GPs including pre-tests of the study questionnaire and potential need for sample size adjustment. The pilot study will essentially function as a “scale model” of one study cycle of the planned pragmatic, two-arm, clustered randomised controlled trial (cRCT). For each study cycle, ten GP practices will be randomised (1:1) into either the intervention or control group. A study cycle is defined as a period of 5 weeks of face-to-face, practice-based data collection in people with IHD immediately following consultation with GPs who have been trained (intervention group, *n* = 5 practices) and a period of 5 weeks of face-to-face data collection in people with IHD immediately after consultation with GPs who have not been trained (control group, n = 5 practices). Per practice, approximately twelve people with IHD will be recruited, resulting in a pilot sample of 120 people with IHD.

A process evaluation with semi-structured, problem-centred individual interviews with GPs of the pilot study and with their patients with IHD who received PA advice will also be conducted. The aim is to understand: A) to what extent training contents could be implemented into practice, which factors facilitated or hampered the transfer, and how GPs experienced the delivery of very brief PA advice, and B) patients’ experiences with received advice, and their met and unmet needs. Experiences with the study procedures will be explored in both groups. Approximately six to eight interviews per group are expected to be sufficient. Data collection will continue until reaching data saturation [42] (for methodological details see WP2). Based on the insights gained from these interviews, study processes and the training manual will be further refined.

### Analyses WP5

The process evaluation data will be analysed as described in WP2.

### Current status

At the time of submission of this protocol, WP 5 is still ongoing and will be finished by the end of 2024.

## Phase III) Main evaluation study by means of a pragmatic, two-arm cluster randomised controlled trial (cRCT), including process evaluation and accompanying health economic research

### WP6: Main evaluation study

Following successful implementation of WP1 to WP5, WP6 aims to evaluate the effectiveness of the developed brief, single-session, tailored GP training in increasing patient-reported proportions of GP-delivered brief advice on PA to people with IHD.

The primary outcome will be the (1) proportion of people with IHD who report having received PA advice during a routine consultation with their GP. Secondary outcomes will include the proportion of patients reporting (2a) the assessment of their PA level by the GP, (2b) the receipt of a concrete recommendation on PA (e.g., the receipt of concrete information on duration, frequency or type of PA exercise and/or patient information leaflets with information on PA), (2c) receipt of an offer for a follow-up appointment with the GP to monitor or discuss the patients’ PA level, and (2d) in the subgroup of patients with IHD who reported that they had a conversation with their GP on PA: satisfaction with the advice received. Another outcome will be (3) the short-term effect of the training on GP-reported attitude towards, opportunity and knowledge of, as well as practical skills in the delivery of PA advice, according the COM-B theory [35].

For these purposes, a pragmatic, two-armed cRCT with 1:1 randomisation will be conducted in GP practices. Since details of WP6 may change after WP5 has been completed, the design of WP6 will only be described briefly.

Primary and secondary outcomes will be collected over a five-week period of face-to-face, practice-based data collection in people with IHD immediately following their consultation with GPs who have received the developed training on PA advice (intervention group). Data collection in people with IHD immediately after their consultation with untrained GPs (control group) will also conducted in a five-week period, resulting in a total period of 10 weeks of data collection for one full study cycle (Fig. 2).

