**Phase III: Main evaluation study by means of a pragmatic, two-arm cluster randomised controlled trial (cRCT), including process evaluation and health economic accompaniment** (study years 4–5)			
WP 6: Main evaluation study	24 months	*Primary research question*: • What is the proportion of people with IHD who report receiving brief advice on PA during a routine consultation with their GPs of the intervention group compared to GPs of the control group? *Secondary research questions*: • What is the proportion of people with IHD whose current PA level was assessed by the GP? • What is the proportion of people with IHD who received specific recommendations or information about duration, frequency, or type of PA exercise and/or patient information sheets with information about PA? • What is the proportion of people with IHD who received an offer for a follow-up appointment with the GP to monitor or discuss PA level? • How satisfied are the people with the advice they received (if so)? *Further research questions*: • What is the short-term training effect on GPs' reported attitude, opportunity, knowledge, and practical skills in providing advice on PA? *Process evaluation*: • What are facilitators and barriers of GPs to the routine implementation of PA advice, including reimbursement strategies for its routine provision? • What are the patients' experiences with the GP advice they received (if so; including facilitators and barriers for the implementation of the advice by their GPs)? *Accompanying health economic research*: • Which preferences do people with IHD have regarding outcomes on increased PA? • Is it adequate to assess health care utilisation in IHD patients with the developed questionnaire?	• Full pragmatic, two-arm cRCT with randomisation (1:1); data collection in 50 GP practices (25 per study arm) and in a study sample of *n* = 300 people with IHD per study arm *Process evaluation*: • Semi-structured qualitative interviews with people with IHD who received PA advice from a GP of the intervention group (*n* = 30–40) • Qualitative process evaluation with GPs (*n* = 8–12) *Health economic accompaniment*: • Evaluation of the DCE in people with IHD of the control group of the cRCT (see WP4, *n* = 300) • Piloting of the health care utilisation questionnaire in patients of the control group of the cRCT (*n* = 300)

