**Fig. 2 Fig2:**
[figure not shown]
Study flow of the planned cluster randomised controlled trial (O = no training). A study cycle consists of 10 weeks of data collection: 5 weeks patients of “control” and 5 weeks in patients of “intervention” general practitioners (GPs). In total there will be five cycles resulting in 50 practices (25 intervention and 25 control practices)

As described in WP1, we calculate with an estimate of 20% of patients who report the receipt of brief PA advice during their GP visit without the GP having been trained. Another study showed that a brief single-session GP training can increase patient-reported rates of GP-delivered stop-smoking advice by 20%-points on average [52]. Training GPs to deliver PA advice might be more challenging, e.g., because PA recommendations are more complex than simple advice on smoking cessation methods. Training on PA advice is thus declared to have a clinically relevant effect if higher rates of delivered PA advice of at least 13%-points can be achieved in the intervention group (33%) as compared to the control group (20%), corresponding to an odds ratio of 1.97. Sample size calculation is based on the standard χ2-test in a four-fold-table and a multiplicative correction (= 1 + 0.05*(12–1) = 1.55, i.e., assuming an intraclass correlation coefficient of 0.05 and twelve IHD patients/practice) by the design effect to account for clustering. Including a total of 600 people with IHD in 50 practices (25 per study arm) will yield a power of at least 85% in the primary analysis of the intervention effect in a logistic regression model with a random intercept effect accounting for the nested design, while adjusting for patient and practice characteristics.

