### Analyses WP6

A detailed study and analysis protocol will be published at OSF prior to the statistical analyses. The data analysis will follow the hierarchical clustered structure of the study (patients nested within practices). Logistic mixed-effects regression models will be applied to analyse the primary outcome, with a fixed effect for the group (intervention versus control) and a random intercept for the practices. The same model will be used on the secondary outcomes. Models will be adjusted for pre-defined potential confounders: patients’ age, sex, education, level of PA, and BMI. All patients will be included in an intention-to-treat analysis. Based on experiences from another cRCT [52], missing data on the primary outcome is assumed to be minimal as data will be collected through face-to-face interviews. However, multiple imputation will be applied to impute missing data if needed.

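### Satisfaction (outcome 2d) is put through the arm-comparison model in a post-randomisation subgroup whose membership the training is meant to change, so that contrast is not protected by randomisation

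*Protocol article*

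**What the plan says.** All references are to the Protocol article.

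- **Outcome.** The section WP6: Main evaluation study lists satisfaction as secondary outcome 2d, measured "in the subgroup of patients with IHD who reported that they had a conversation with their GP on PA: satisfaction with the advice received". Outcomes 2a to 2c carry no such restriction.
- **Model.** Analyses WP6 describes a logistic mixed model for the primary outcome, "with a fixed effect for the group (intervention versus control) and a random intercept for the practices", and continues: "The same model will be used on the secondary outcomes". Outcome 2d is not excepted.
- **Covariates.** The models adjust for patients' "age, sex, education, level of PA, and BMI".
- **Analysis set.** The same section states: "All patients will be included in an intention-to-treat analysis". Again 2d is not excepted.
- **Aim.** WP6 is to evaluate the "tailored GP training in increasing patient-reported proportions of GP-delivered brief advice on PA to people with IHD". The sample size paragraph plans for 20% of control patients and 33% of intervention patients reporting advice.
- **Table 1.** The WP6 row asks how satisfied patients are with advice, if they received any. It names no comparator, and it conditions on advice where the WP6 text conditions on a conversation.

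**The concern.** Whether a patient had a conversation about physical activity is known only after the consultation, and so after the practice was randomised. It lies close to the primary outcome, which the training is designed to raise. If the training works, the intervention subgroup contains patients whose counterparts in control practices had no such conversation and are left out. The two subgroups are then different selections of patients, and the arm term in the model mixes that difference with any real change in how well advice was given.

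The five covariates cannot be relied on to remove this. A patient's motivation, and the GP's reason for raising the subject with one patient rather than another, are not among them.

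The abstract and the Conclusion tie the value of the training to the quality of advice as well as its frequency. Satisfaction is a natural reading of quality, so a biased arm effect on 2d could support or undercut that part of the message.

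**Working it through.** **1. What the plan's own figures cover.** No rate, sample size or power is stated for 2d. The planned rates belong to the primary outcome, and their odds ratio reproduces: (0.33/0.67)/(0.20/0.80) = 1.97, as stated. They are rates of *advice*. The rate of any *conversation*, which decides entry to 2d, is not given.

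**2. Reading the rules together.** WP6 restricts 2d to patients with a conversation. Analyses WP6 gives the secondary outcomes the model with the arm term and includes all patients. Taken literally, 2d is tested between arms, and it cannot be both restricted to a subgroup and analysed in everyone.

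**3. Share of the intervention subgroup present only because of the training.** Let p_C and p_T be the conversation rates. Assume that the training never removes a conversation. The share is s = (p_T − p_C)/p_T. With 300 patients per arm, a rise of 13 points (the planned difference for advice, borrowed here) and three assumed starting rates:

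| Control to intervention rate | Patients in subgroup | s |
|---|---|---|
| 20% to 33% | 60 and 99 | 13/33 = 39.4% |
| 40% to 53% | 120 and 159 | 13/53 = 24.5% |
| 60% to 73% | 180 and 219 | 13/73 = 17.8% |

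**4. Resulting bias.** Let a be satisfaction in patients who would have had the conversation anyway, b satisfaction in those added by the training, and g a true gain given to everyone in the intervention arm. The subgroup contrast is g − s(a − b). All values of a, b and g below are assumptions.

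- a = 80%, b = 60%, g = 0. The contrast is −0.394 × 20 = −7.9 points, −0.245 × 20 = −4.9 points, or −0.178 × 20 = −3.6 points. The true effect is zero.
- Same a and b, g = 5 points. The contrast is 5 − 7.9 = −2.9, 5 − 4.9 = +0.1, or 5 − 3.6 = +1.4 points. The sign is wrong only in the first case, but the gain is understated in all three.
- a = 80%, b = 95%, g = 0. At 20% to 33% the contrast is +0.394 × 15 = +5.9 points, so the bias can also flatter the training.
- If the training changes neither how many nor which patients have a conversation, or if added patients are as satisfied as the others, the bias is zero.

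**5. Against sampling error.** In the first case of step 4, with 60 and 99 patients, the standard error before clustering is √(0.80 × 0.20/60 + 0.721 × 0.279/99) = √(0.00267 + 0.00203) = 6.9 points. The 7.9-point bias is about 1.1 standard errors.

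**6. An all-patient composite.** Take conversation and advice as the same event at 20% and 33%, with 80% satisfied in both arms (assumed). The proportion advised and satisfied is 0.20 × 0.80 = 16.0% against 0.33 × 0.80 = 26.4%. It rises by 10.4 points from frequency alone.

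**The case against.** The arm comparison of 2d is read from one general sentence, not from the definition of the outcome. Table 1 asks the question neutrally. WP6 is described only in brief, may change after the pilot, and is to be followed by a detailed analysis protocol. The satisfaction scale is not shown, so it is not even clear that a logistic model suits it. Satisfaction is also the last of four secondary outcomes. Outcomes 2a to 2c measure elements of quality in all patients and are untouched, as is the primary result.

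This limits the weight of the point but does not remove it. The sentence on the secondary outcomes is a rule that the article itself states, and both it and the intention-to-treat sentence need an exception for 2d.

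The objection to larger claims does stand. A reader might take 60 and 99 as the planned size of the subgroup. They are not: 20% and 33% are advice rates, and WP1 ties its 20% to advice containing all three elements of the method. The Background describes routine advice as often unspecific talk, so conversations may well be commoner in control practices. If the training mainly turns existing conversations into structured advice, the conversation rate may hardly move. With numbers of this order, the likeliest result for 2d is also an inconclusive one, not a firm finding of harm or benefit.

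**Conclusion.** The point holds as a flaw in a secondary analysis. As written, the plan tests the arms within a subgroup formed after randomisation that the training is meant to alter, and it makes an intention-to-treat statement that cannot apply to 2d.

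Neither the direction nor the size of the bias can be known from the protocol. Under the assumptions shown (a 13-point rise in conversations, no conversation removed by the training, a 20-point satisfaction gap), the spurious difference is about 8, 5 or 4 points for starting rates of 20%, 40% or 60%.

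Three stronger readings are not supported:

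- That the training *creates* the subgroup. It enlarges and changes it: even at 20% to 33%, 60 of the 99 intervention patients would be in it without training.
- That the comparison *will* point the wrong way. This happens only for some assumed values, and the protocol gives no satisfaction figures.
- That the sponsor intends a causal claim about quality from 2d. No passage says so. The risk is that an unlabelled arm effect invites that reading.

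**What to change.** 1. In Analyses WP6, except 2d from the sentence applying the primary model to the secondary outcomes and from the intention-to-treat sentence.
2. State that satisfaction will be reported by arm descriptively, with the number of patients contributing in each arm, labelled as a non-randomised comparison without causal interpretation.
3. Use one definition of the subgroup, either a conversation or receipt of advice, in both Table 1 and the WP6 outcome list.
4. If a randomised comparison involving satisfaction is wanted, add receipt of advice together with satisfaction (yes/no) in all analysed patients as a supplementary outcome. Fix the satisfaction cut-point in advance and read the result beside the primary outcome, because it rises with advice frequency alone. It does not replace 2d and does not answer the question in Table 1.

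Items 1 to 3 change wording only, and need no new data or patients. Item 4 also needs a decision on the cut-point. The article states that WP6 had not begun at submission, and the promised analysis protocol is a natural place to record the change.
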